### Sample size calculation

Currently, there is no unified standard for sample size calculation in MEG acupuncture research (37, 40). We will therefore enroll 40 healthy volunteers (20 per group). This sample size was informed by prior neuroimaging studies (41), in which 12–24 participants per group were used to examine brain activation differences between verum and sham acupuncture. Accounting for an anticipated 20% dropout rate, complete data are expected from at least 32 participants (16 per group).

### Randomization

Participants will be randomly assigned to the verum acupuncture (VA) group or the sham acupuncture (SA) group in a 1:1 ratio. The random allocation sequence will be generated using block randomization, stratified by sex, to ensure a balanced distribution of male and female participants across both groups. Allocation concealment will be maintained by having the research coordinator obtain the participant’s intervention assignment from sequentially numbered, opaque, sealed envelopes immediately before the first intervention session, and communicate this information exclusively to the acupuncturist.

### Blinding

A single-blind design will be employed, whereby participants will be blinded to their group allocation. In addition to participant blinding, the outcome assessors, MEG technicians, and data analysts will all be blinded to group assignment. Only the acupuncturist performing the needling will be aware of the allocation. At the end of the study, blinding success will be assessed by asking each participant to guess their group allocation (verum, sham, or “do not know”). Responses will be quantified using Bang’s Blinding Index (BI).

### Interventions

#### VA group

The VA group will receive acupuncture at the standard acupoints of the Xingnao Kaiqiao protocol. The acupoints include Neiguan (PC6, bilateral), Shuigou (GV26), Sanyinjiao (SP6, bilateral), XiaJiquan (Lower HT1, bilateral), Chize (LU5, bilateral), Weizhong (BL40, bilateral), Lianquan (CV23), and PangLianquan (Beside CV23, bilateral). Acupoint localization will follow the WHO Standard Acupuncture Point Locations in the Western Pacific Region (2020 edition). Disposable silver acupuncture needles (0.30 × 40 mm; Hwato Brand, Suzhou Medical Appliance Factory Co., Ltd., China) will be used. All acupuncture procedures will be performed by a licensed acupuncturist with at least 5 years of clinical experience.

The acupuncture procedure will follow the standardized Xingnao Kaiqiao acupuncture protocol (42), with the CV23 and Beside CV23 techniques based on the research group’s prior study published in a JAMA Network Open randomized clinical trial (10). Participants will be positioned supine. The single-acupoint sequence will be performed first, followed by the multi-acupoint sequence. The acupuncturist will needle the points in the following order: Neiguan (PC6), Shuigou (GV26), Sanyinjiao (SP6), XiaJiquan (Lower HT1), Chize (LU5), Weizhong (BL40), Lianquan (CV23), and Beside CV23. The locations and needling techniques for each acupoint are described in Table 1 and Figure 3.

**Table 1 tab1:** Acupoint locations, needling techniques, and needle retention times in the VA group.

Acupoint name	Location	Needling technique	Retention
Neiguan (PC6, bilateral)	On the anterior forearm, 2 cun proximal to the palmar wrist crease, between the palmaris longus and flexor carpi radialis tendons	Perpendicular insertion 0.5–1.0 cun; twirling-rotating combined with lifting-thrusting reducing method; bilateral simultaneous manipulation for 1 min	No retention
Shuigou (GV26)	On the face, at the junction of the upper one-third and middle one-third of the philtrum	Oblique insertion 0.3–0.5 cun toward the nasal septum; sparrow-pecking reducing method until the eyes become moist or tearing occurs	30 min
Sanyinjiao (SP6, bilateral)	On the medial lower leg, 3 cun above the medial malleolus, posterior to the medial tibial border	Perpendicular insertion 1.0–1.5 cun; twirling-rotating reinforcing method; bilateral simultaneous manipulation for 1 min	30 min
XiaJiquan (Lower HT1, bilateral)	On the anterior upper arm, 1–2 cun inferior to Jiquan (HT1), along the line connecting Jiquan (HT1) and Shaohai (HE3)	Perpendicular insertion 1.0–1.5 cun; lifting-thrusting reducing method until 3 involuntary limb twitches are elicited	No retention
Chize (LU5, bilateral)	On the cubital crease, radial to the biceps brachii tendon	Perpendicular insertion 0.5–0.8 cun with elbow flexed at 120°; lifting-thrusting reducing method until 3 involuntary forearm twitches	No retention
Weizhong (BL40, bilateral)	At the midpoint of the popliteal crease, between the biceps femoris and semitendinosus tendons	Perpendicular or oblique insertion 1.0–1.5 cun with leg elevated and extended; lifting-thrusting reducing method until 3 involuntary limb twitches	No retention
Lianquan (CV23)	On the anterior midline, in the depression above the hyoid bone, superior to the thyroid cartilage	Perpendicular insertion 2.0 cun; lifting-thrusting and twirling-rotating to achieve *deqi*	30 min
PangLianquan (Beside CV23, bilateral)	0.5 cun lateral to Lianquan, in the depression above the notch of the thyroid cartilage	Perpendicular insertion 1.0–1.5 cun; lifting-thrusting and twirling-rotating to achieve *deqi*	30 min

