#### SA group

Considering the practical constraints of the Xingnao Kaiqiao multi-acupoint protocol, in which spring-type placebo needles or skin-adhesive sham devices are not feasible and may compromise blinding, the SA control was designed based on published international acupuncture clinical trial protocols (10). The SA group will receive superficial needling at non-acupoints located 1 cun (approximately 20 mm, using the participant’s proportional measurement) lateral to each corresponding verum acupoint. The same type of needle (0.30 × 40 mm; Hwato Brand) will be used, and the procedure will be performed by the same qualified acupuncturist.

At each sham acupoint, the needle will be inserted superficially to a depth of 0.2–0.3 cun (approximately 4–6 mm), sufficient only to suspend the needle in the skin. No manual manipulation will be applied, and participants should not experience *deqi* sensation. Bilateral simultaneous needling and needle retention durations will be identical to the VA group. The single-acupoint sequence will be performed first, followed by the multi-acupoint sequence, consistent with the VA protocol.

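### At the protocol's own conversion, the fixed CV23 depth of 2.0 cun is about 40 mm, the full length of the only needle named

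*Protocol article*

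**What the plan says.** Four statements in the Interventions section of the protocol article have to be read together.

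- **Depth.** Table 1 (VA group) gives CV23 as "Perpendicular insertion 2.0 cun; lifting-thrusting and twirling-rotating to achieve" *deqi*, with 30 min retention. It is the only row with a single depth; the other seven give a range.
- **Needle.** The VA group section names one product: "Disposable silver acupuncture needles (0.30 × 40 mm". The SA group section repeats the size: "The same type of needle (0.30 × 40 mm; Hwato Brand) will be used". No other length appears.
- **Size of a cun.** In the SA group section the sham points are "located 1 cun (approximately 20 mm", using the participant's "proportional measurement) lateral to each corresponding verum acupoint". The sham needle is "inserted superficially to a depth of 0.2–0.3 cun (approximately 4–6 mm". The conversion is thus applied to insertion depth as well as to distance along the skin.
- **Source of the technique.** The VA group section describes the general procedure as standardized, "with the CV23 and Beside CV23 techniques based on the research" group's earlier randomized trial. That trial is cited but its needling details are not reproduced.

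**The concern.** Each statement is unremarkable alone. Together they ask the acupuncturist to insert about the whole of the named needle at CV23, a midline point above the hyoid bone, and to lift, thrust and rotate it there before leaving it in for half an hour. No other point in Table 1 comes near the length of the needle.

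Two things are at stake. The first is safety: the recipients are healthy volunteers with no therapeutic need. Under Assessment timepoints, CV23 is needled once in the single-acupoint sequence and again in the multi-acupoint sequence. With 20 participants planned in the VA group, that is up to 20 × 2 = 40 occasions. The second is fidelity: an acupuncturist who prefers to keep some shaft outside the skin must depart from Table 1 by an amount the document does not set. The depth delivered may then differ from the one specified, and between participants. Anyone replicating the protocol meets the same choice.

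**Working it through.** **Inputs**

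- CV23 depth: 2.0 cun (Table 1).
- Needle length: 40 mm (VA group and SA group sections), read here as shaft length. This is the reading most favourable to the protocol; if 40 mm included the handle, the shaft would be shorter.
- Conversion: approximately 20 mm per cun (SA group section).

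**Reproducing the protocol's own conversion.** For sham depth, 0.2 × 20 = 4 mm and 0.3 × 20 = 6 mm, which match the stated 4–6 mm. In reverse, 4/0.2 = 20 and 6/0.3 = 20 mm per cun. The factor for depth is therefore the same as the factor for lateral distance, and no printed conversion is wrong.

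**Formulas.** Depth in mm = cun × 20. Shaft exposed = 40 − depth in mm.

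**Each row of Table 1 at its greatest depth**

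| Point | Greatest depth (cun) | Depth (mm) | Shaft exposed (mm) |
|---|---|---|---|
| PC6 | 1.0 | 20 | 20 |
| GV26 | 0.5 | 10 | 30 |
| SP6 | 1.5 | 30 | 10 |
| Lower HT1 | 1.5 | 30 | 10 |
| LU5 | 0.8 | 16 | 24 |
| BL40 | 1.5 | 30 | 10 |
| **CV23** | **2.0** | **40** | **0** |
| Beside CV23 | 1.5 | 30 | 10 |

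At the matched sham point the depth is at most 6 mm, so 40 − 6 = 34 mm stays outside. The problem is confined to the verum side.

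**Sensitivity to the factor.** The protocol calls the conversion approximate and gives no range. The values from 18 to 22 mm per cun below are my assumption, for illustration only.

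| mm per cun (assumed) | CV23 depth (mm) | 40 − depth (mm) | Exposed at a 1.5 cun point (mm) |
|---|---|---|---|
| 18 | 36 | +4 | 40 − 27 = 13 |
| 19 | 38 | +2 | 40 − 28.5 = 11.5 |
| 20 | 40 | 0 | 40 − 30 = 10 |
| 21 | 42 | −2 | 40 − 31.5 = 8.5 |
| 22 | 44 | −4 | 40 − 33 = 7 |

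A negative figure means that the stated depth is greater than the needle length. Over this range the CV23 margin lies on either side of zero, while the next deepest points keep at least 7 mm.

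**The case against.** The strongest reply is that nothing here is shown to be impossible. At the stated factor the depth equals the needle length and does not exceed it, and a slightly smaller cun leaves a few millimetres. If 40 mm is the shaft, the handle stays outside the skin even at full depth. The article sets no minimum exposed length, so how much shaft manipulation and retention need is a clinical judgement. All of this stands, and it is why the point is a mismatch and not an impossibility. It does not remove the mismatch, because the approximation can as easily take the depth past the end of the needle.

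A second reply is that the CV23 technique comes from a prior trial that may settle the matter, and that a condensed article may leave limits for single points to the full protocol. The first part is fair, and it makes that trial the place to check. The second carries less weight. The article itself states the depth, the needle and the conversion, and it repeats the needle size for the sham group, which counts against an unlisted longer needle.

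A third reply is that all needling is done by a licensed acupuncturist with five or more years in practice. That makes literal full insertion less likely, but it does not correct the text, and it leaves the delivered depth to individual discretion.

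A reader might also infer that 2.0 cun is a misprint, since every other row leaves more room. The documents do not support that. Comparing margins shows that CV23 is unusual, not that its depth is a slip; the needle could equally be the wrong element.

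**Conclusion.** The mismatch is real and should be corrected. At the protocol's own conversion, the CV23 depth is about 40 mm on a 40 mm needle, leaving about 0 mm of shaft, with a few millimetres of uncertainty either way. Every other row leaves at least 10 mm at the same factor. The conclusion rests on applying about 20 mm per cun to depth, as the SA group section does, and on reading 40 mm as shaft length.

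Three stronger readings go too far. The document does not establish that the depth cannot be reached, since the margin straddles zero. No number or share of affected participants can be derived, since no distribution of cun size is given, and proportional measurement is stated for the lateral distance and not repeated for depth. Nor does the point touch the statistical plan: sample size, endpoints and analysis are unaffected.

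**What to change.** First check the CV23 depth and needle against the prior trial that the VA group section cites for the technique. Then do one of the following:

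- If 2.0 cun is intended, specify a needle clearly longer than 40 mm for CV23. Use the same needle at its matched sham point, so that the two groups still share one needle type.
- If 2.0 cun is not intended, correct the CV23 row of Table 1 to a value or range clearly below 2.0 cun and keep the 40 mm needle.

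In both cases state a maximum insertion depth in mm, set by the clinical lead. The factor in the article is too approximate to derive a precise needle length or depth limit from it, so none is proposed here.

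The cost is one check against the cited trial and an edit to one table row or to one needle specification.

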**Figure 3 fig3:**
[figure not shown]
Location of verum acupoints and sham acupoints.

#### SA group

Considering the practical constraints of the Xingnao Kaiqiao multi-acupoint protocol, in which spring-type placebo needles or skin-adhesive sham devices are not feasible and may compromise blinding, the SA control was designed based on published international acupuncture clinical trial protocols (10). The SA group will receive superficial needling at non-acupoints located 1 cun (approximately 20 mm, using the participant’s proportional measurement) lateral to each corresponding verum acupoint. The same type of needle (0.30 × 40 mm; Hwato Brand) will be used, and the procedure will be performed by the same qualified acupuncturist.

At each sham acupoint, the needle will be inserted superficially to a depth of 0.2–0.3 cun (approximately 4–6 mm), sufficient only to suspend the needle in the skin. No manual manipulation will be applied, and participants should not experience *deqi* sensation. Bilateral simultaneous needling and needle retention durations will be identical to the VA group. The single-acupoint sequence will be performed first, followed by the multi-acupoint sequence, consistent with the VA protocol.

### Assessment procedures

#### Washout period determination

Based on the research group’s pilot work, a washout period study will be conducted to determine the duration required for MEG signals to return to baseline following acupuncture. Shuigou (GV26) was chosen as the reference acupoint because it receives the strongest stimulation in the XNKQ protocol (sparrow-pecking reducing method until tearing) and is expected to produce the longest-lasting central responses. Using this point therefore yields a conservative estimate that should be sufficient for the other acupoints. MEG signals will be assessed at 0.5 h, 1 h, and 2 h post-acupuncture to evaluate the decay time of the acupuncture effect. The identified washout period will be used as the inter-acupoint interval during the single-acupoint sequence.

#### Assessment timepoints

The assessment will proceed in the following sequence. First, during the baseline period, participants will complete language tasks with simultaneous MEG recording. Second, a resting-state MEG scan will be performed after the language tasks and before the first acupuncture intervention. Third, the acupuncture state assessments will follow a sequence of single-acupoint needling first and then multi-acupoint needling.

In the single-acupoint sequence, after completing the language task and resting-state MEG scans, each acupoint will be needled individually, completing a total of seven acupuncture-state data acquisitions (CV23 and its auxiliary acupoints Beside CV23 are needled simultaneously and recorded as a single acquisition). For acupoints requiring 30-min needle retention (GV26, SP6, CV23, and Beside CV23), MEG data will be collected during the retention period, followed by a resting-state acquisition after needle removal. For acupoints without needle retention (PC6, HT1, LU5, and BL40), an immediate post-needling MEG acquisition will be performed. The interval between successive acupoints will follow the washout period determined in the pilot study.

In the multi-acupoint sequence, after all single-acupoint sessions are completed and the washout period has elapsed, a resting-state MEG scan will be performed. Subsequently, all acupoints will be needled simultaneously as a group, with MEG data collected during the retention period. After needle removal, a final resting-state MEG scan will be conducted to assess the overall central mechanism of the full Xingnao Kaiqiao acupuncture.

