### Outcome measures

#### Primary outcome

The primary outcome is the change in MEG signals before and after acupuncture intervention. MEG data will be collected during the resting state, acupuncture state, and language task state to evaluate the central effects of acupuncture. Specific MEG metrics include power spectral density (PSD) across different frequency bands (delta: 1–4 Hz, theta: 4–8 Hz, alpha: 8–13 Hz, beta: 13–30 Hz, gamma: 30–80 Hz), source-space neural activity, and whole-brain functional connectivity.

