#### Task-state analysis

For task-state data, brain activity will be extracted from event-related epochs spanning −500 ms to 1,500 ms relative to stimulus onset, with baseline correction applied from −200 ms to 0 ms. Source localization methods will be used to reconstruct brain activation at different time windows, thereby obtaining dynamic source-space responses during task execution. The analysis will focus on changes in activated brain regions during stimulus processing, phonological and language processing, and other task-related cognitive stages across different time points, thereby revealing the influence of acupuncture intervention on neural activity.

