### Statistical analysis

For the resting-state PSD values, source-space neural activity, and whole-brain functional connectivity indices, both within-group and between-group comparisons will be performed. For within-group comparisons of pre- and post-acupuncture paired data, paired *t*-tests will be used. For between-group comparisons of the VA and SA groups, independent-sample *t*-tests will be employed. In whole-brain source-space statistical analyses, permutation-based cluster correction (≥5,000 permutations) will be applied to control for multiple comparisons and to identify brain regions with statistically significant differences.

For task-state data, time-window-based statistical methods will be used to compare brain activation intensity at different post-stimulus stages (time windows from 0 to 1,000 ms, in 100-ms steps). Linear mixed models will be applied to analyze condition effects and their interactions.

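### Language tasks are recorded only before any needling, so the task-state part of the before/after primary outcome cannot be estimated

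*Protocol article*

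**What the plan says.** The Assessment timepoints section sets out an ordered sequence. It begins: "First, during the baseline period, participants will complete language tasks with simultaneous MEG recording". Then: "Second, a resting-state MEG scan will be performed after the language tasks and before the first acupuncture intervention". Needling follows: "after completing the language task and resting-state MEG scans, each acupoint will be needled individually". For points with needle retention, "MEG data will be collected during the retention period, followed by a resting-state acquisition after needle removal"; for the others, "an immediate post-needling MEG acquisition will be performed". The multi-acupoint part has a resting scan beforehand, a recording during retention and a closing resting scan. The Resting-state recording section provides a before/after pair for rest and for nothing else.

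The outcome and analysis sections read differently. The primary outcome is the change in MEG signals from before to after acupuncture, and of its data the protocol says: "MEG data will be collected during the resting state, acupuncture state, and language task state to evaluate the central effects of acupuncture". The Task-state analysis section ends by promising to study task activity, "thereby revealing the influence of acupuncture intervention on neural activity". For task data the Statistical analysis section offers comparisons over 100-ms windows and adds: "Linear mixed models will be applied to analyze condition effects and their interactions". Two Discussion sections, on language task paradigms and on *deqi*, also expect task recordings to show effects of acupuncture or of needling sensation.

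**The concern.** A before/after outcome needs a measurement on each side of the intervention. For the language tasks the schedule supplies only the first. The primary outcome and the task analysis therefore claim something that the data cannot deliver.

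Two things are at stake. The task-state component of the primary outcome would have to be left empty, or filled with something else once the data are known. And if the arms were compared on task data, a significant result could be reported as an effect of acupuncture although no needle had been placed when the data were recorded. The *deqi* question has the same flaw: sensation is rated after the tasks are over, so a correlation could at most say whether earlier task activity predicts later sensation, not whether sensation alters task activity.

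**Working it through.** **Inputs (Protocol article).** 40 enrolled, 20 per group, 20% dropout (Sample size calculation); sequence of recordings (Assessment timepoints); trial timings (Language tasks); ten windows from 0 to 1,000 ms (Statistical analysis). No alpha, power, effect size or SD is given, so those used below are assumptions.

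**Step 1. The plan's own figure.** 40 × (1 − 0.20) = 32, or 16 per group. This reproduces the stated number of expected completers.

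**Step 2. List the recordings in order.**

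| Order | Recording | Relative to needling | Language task? |
|---|---|---|---|
| 1 | Picture naming and repetition | before | yes |
| 2 | Resting scan | before | no |
| 3 | Seven single-acupoint acquisitions: 3 during retention, each followed by a resting scan; 4 immediately after needling | during/after | none named |
| 4 | Resting scan after washout | after single points | no |
| 5 | Multi-acupoint recording during retention | during | none named |
| 6 | Final resting scan | after | no |

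Task sessions before needling: 1 (2 tasks × 100 trials). During or after needling: 0. The Language tasks section puts a 5-min resting recording ahead of the tasks, whereas the sequence puts the resting scan after them. Both precede needling, so the count stands.

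**Step 3. What can be estimated.** For participant i and task k the change is Y(post) − Y(pre). Y(post) does not exist for any i or k, so neither a within-group change nor a group-by-time interaction is available. What remains is mean Y(pre) in the verum (VA) group minus mean Y(pre) in the sham (SA) group. Randomisation gives this an expected value of zero, whatever the effect of needling. In the stated order the tasks even precede disclosure of the allocation, since the envelope is opened just before the first intervention session.

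**Step 4. Illustration.** 20,000 simulated two-sample t-tests for each effect size, 16 per group, two-sided alpha 0.05, SD 1, with a standardised effect d that acts only after needling:

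| d | Rejection rate, tasks before needling only | Power if tasks were also recorded after needling (post-needling data compared) |
|---|---|---|
| 0 | 0.049 | 0.049 |
| 0.5 | 0.050 | 0.28 |
| 1.0 | 0.050 | 0.78 |
| 1.5 | 0.051 | 0.98 |

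As scheduled, power equals alpha at every d. An analytic check of the last column gives 0.29, 0.81 and 0.99 for d = 0.5, 1.0 and 1.5.

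**Step 5. Time for one repeat.** Naming: 100 × (0.5 + 1.5 + 3.0) s = 500 s = 8.3 min. Repetition: 100 × (0.5 + 0.66 + 1.5 to 2.0 + 1.0) s = 366 to 416 s = 6.1 to 6.9 min. Together 866 to 916 s, or 14.4 to 15.3 min, plus breaks.

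**The case against.** **The article condenses a fuller protocol, and the flowchart and sequence figures are not shown.** A post-needling task in those figures cannot be ruled out. But their captions mention needling, retention with MEG recording and washout, and no task. The written sequence runs through to the last scan, and an analysis plan cannot supply a measurement that was never scheduled. If a figure did show such a task, the text would still need correcting.

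**The recording during retention might include a task.** Its content is not described, and the Background names task activity during acupuncture as a gap in the literature. However, the protocol calls these acupuncture-state acquisitions, and the Abstract and the Primary outcome section list that state separately from the language task state.

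**Baseline tasks have a use of their own.** This stands. The Background describes a normative reference for later work in patients, and the Abstract's aim for language task states is exploratory. Recordings before needling serve both.

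**Stronger readings that the documents do not support.** A reader might infer that a verum–sham test on task data is planned and would produce a false acupuncture effect with probability 1 − 0.95^20 = 0.64 over 2 tasks × 10 windows. The t-tests between arms are attached to resting-state power, source activity and connectivity; for task data only window comparisons and mixed models with undefined conditions are named, and a condition could be task or window. The 0.64 also assumes one uncorrected test per window and independence. With equal pairwise correlation of 0.5 it is 0.42, and at 0.8 it is 0.23; the documents give no value. Cluster correction is stated for whole-brain source-space analyses, which may cover the task analysis. Nor does it follow that the trial as a whole fails to answer its question.

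**Conclusion.** The contradiction is real and confined to the task state. On the written schedule 0 of 2 tasks have a post-needling recording, so the task-state part of the primary outcome is not estimable, and statements that task data will show effects of acupuncture or *deqi* cannot be supported. Any verum–sham contrast of task data, if made, would carry no information about acupuncture. This rests on reading the written sequence as complete, which its wording and the figure captions favour. The simulated figures illustrate the point under an assumed alpha and SD; the conclusion does not depend on them. The resting-state and acupuncture-state outcomes and the descriptive use of the baseline tasks stand. The correction is needed before results are reported, because the primary outcome is involved.

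**What to change.** **If data collection is complete.** The stated window is February to July 2026 and the article is dated 18 August 2026, so this is the likelier case. Confine the change-based primary outcome to the resting and acupuncture states. Delete the claim about acupuncture from the Task-state analysis section, make no verum–sham contrast of task data, and bring the two Discussion sections into line. Report the tasks as a descriptive baseline map pooled over both arms (up to n = 40), and state what the conditions in the mixed model are. The cost is wording, and giving up a claim that the data cannot bear.

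**If participants are still to be scanned.** Repeat both tasks once, in both arms, after the final resting scan, with the same items in a newly randomised order. Define the task outcome as the verum–sham difference in post-needling task response, adjusted for the baseline response. Do not rely on within-arm paired tests, which would mix any acupuncture effect with practice on repeated items. The cost is 14.4 to 15.3 min of recording per participant plus breaks. Parallel item sets would need further naming-agreement and familiarity piloting. A single repeat at the end cannot separate single-point from multi-point effects on language, and participants already scanned would contribute no change.
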